## 7.4 Study visits

This section explains which visits are required, when they should occur and what study procedures should be performed during each visit.

### 7.4.1 Baseline visit

The baseline visit can be a stand alone visit or occur on the same day as the EP study. A subject is enrolled in the study when he/she signs the Informed Consent Form.

At this point, the patient will be assigned a subject number and is considered a subject in the investigation. The following procedures/data collection will be conducted during the baseline visit:

- Verification of all inclusion and all exclusion criteria
- Enrollment
- Subject demographics (e.g., age, gender, height, weight, race)
- Medical history (cardiovascular or related)
- Cardiovascular medications
- NYHA classification
- Blood pressure
- Left ventricular ejection fraction (within last 3 months, otherwise a new measurement should be performed)
- Multi-lead ECG (within last 3 months, otherwise a new ECG should be performed)
- Pregnancy test for women with child-bearing potential
- Echocardiographic evaluation (if available within last 3 months, otherwise not collected )
- Venous blood sample to determine heart failure severity (NTproBNP, creatinine and hemoglobin)
- Magnetic Resonance Imaging (MRI) as explained in paragraph below

#### **7.4.1.1 Magnetic Resonance Imaging (MRI)**

Patients will undergo a baseline MRI before scheduled CRT-related surgery (i.e. is dedicated research study or EP procedure or actual CRT implant) to identify the location and transmuralty of any myocardial scar using late gadolinium enhancement-magnetic resonance imaging according to standard hospital practice. In addition, left ventricular end systolic volume (LVESV), left ventricular end diastolic volume (LVEDV) and left ventricular ejection fraction (LVEF) will be determined. MRI can be performed as standard of care or solely for the study.

#### **7.4.2 Electrophysiological (EP) study visit**

The EP study visit can be a stand alone visit or can occur on the same day as the baseline visit. The EP study visit should take place within 3 months after the MRI has been obtained. Patients will undergo standard implant of a biventricular pacing system (Medtronic CRT or CRT-D) or will undergo an EP study before possible CRT-implant. If available in the center, a Finger plethysmography system (eg. model Nexfin, BMEYE B.V.) will be connected to one of the subject's fingers to measure the blood pressure non-invasively. In addition, a multi-lead surface ECG is collected during the whole procedure.

Pacing electrodes (cardiac leads or EP catheters) will be placed in the right atrium (RA) and right ventricle (RV). The coronary sinus will be cannulated, a venogram will be obtained and target vessels for LV stimulation will be identified. An EP-catheter ("Multi-electrode lead") or LV lead will be used for LV pacing. Also a CE-certified LV-quadrupolar lead from Medtronic, when available, can be used in the study as an alternative for the EP-catheter. The temporary LV pacing electrodes (EP catheter or LV lead) will be inserted into the coronary sinus (CS) and then sequentially into each suitable target vein.

Targeted myocardial regions for LV lead/catheter placement are: lateral or posterolateral (Standard vein), posterior (Alternative vein I) and anterior (Alternative vein II). Pacing will be performed at up to three spots simultaneously within the Standard vein - MultiSpot), covering the basal to apical locations when feasible (see figure 4). The leads placed in the alternative veins I and II will be stimulated separately or simultaneously (multi-vein; uni-spot) covering the heart circumferentially. A lateral LAO, RAO and/or AP fluoro-screen shot will be taken to document the different (temporary) lead positions.

A Millar pressure catheter or similar will be introduced via the femoral artery retrograde across the aortic valve into the LV for hemodynamic pressure monitoring. Heparin will be administered to ensure that the activated clotting time is monitored per standard hospital practice. The different pacing settings include simultaneous RV- and LV pacing and are in bipolar or unipolar mode.

The MRI-images will ascertain avoidance of pacing ischemic scar tissue. In addition, paced left ventricular QRS-width may also be used for optimal coronary sinus lead placement [33].

A

MRI

**PROTOCOL**

B

**PROTOCOL (First part)**

Place "Multi-electrode lead" in (~~postero~~)lateral vein position

Start RA-pacing (100 bpm or otherwise highest tolerable rate)

(A) Pacing @ distal electrode. Make sure capture is obtained. If yes, run pacing protocol

(B) Pacing @ mid electrode. Make sure capture is obtained. If yes, run pacing protocol

(C) Pacing @ proximal electrode. Make sure capture is obtained. If yes, run pacing protocol

(D) Simultaneous pace @ all three electrodes  
Run pacing protocol

C

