## 6.4 Minimization of bias

Potential sources of bias in this study may result from selection of subjects, treatment of subjects, and evaluation of study data. Methods incorporated in the study design to minimize potential bias include but are not limited to:

- Subjects will be their own control, and study measurements have been designed to minimize the impact of within-subject temporal variation.
- Subjects will be screened to confirm eligibility for enrollment with defined inclusion/exclusion criteria prior to enrollment (See Section 6.3 Subject Selection)
- Subject demographics will be collected at the enrollment visit on possible differences that may affect primary endpoints.
- Data collection requirements and study procedures will be standardized across all study centers, including identical and calibrated equipment.
- All implanters in the study will be experienced in the placement of LV leads, performing EP procedures, performing LV pressure measurements.
- All study center personnel and Medtronic personnel will be trained on their respective aspects of the study using standardized training materials. All study clinicians will be trained on and required to follow the Clinical Investigational Plan.

In summary, potential sources of bias that may be encountered in this clinical investigation have been considered and minimized by careful study design.

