## E Pacing protocol

## Pacing protocol

- Program optimal AV delay
- Turn pacing 'on' via connection box during 10-15 sec
- Turn pacing 'off' via connection box during 10-15 sec
- Repeat ON/OFF 3 times (so 4 times in total)
- Program other AV delays (+/- 20 ms & +/- 40 ms) and repeat pacing protocol

[figure not shown]

**Figure 4: Description of the pacing protocol.** In A the start of the protocol is depicted which involves imaging of the venous anatomy of the patient. The protocol can be separated into two parts, depending on the patient's anatomy. Part B is similar for every patient while part C or D is patient-dependent. In general, one part consists of BiV or Multivein using one or both of two opposite coronary veins (multivein approach). The other part consists of using up to three LV electrodes (BiV or QuadV) to pace from the (postero)lateral vein (multispot approach). Part E is displaying the pacing procedure for 1 out of total 5 AV delays during which the positive  $dP/dt_{max}$  will be measured. Each setting, as indicated by a horizontal line in the figure, will last 10-15 sec. The repetition of steps is used to increase sensitivity of the positive  $dP/dt_{max}$  measurements. Five AV delays will be assessed: optimal AV, optimal AV delay +/- 20 and +/- 40 ms.

At each pacing site, the evaluation of the effect of CRT will be performed approximately 4 times (repetition) in order to increase signal to noise ratio. Each setting lasts about 20 beats (10-15 sec) interspersed with baseline (AAI; also 20 beats, 10-15 sec) pacing. The heart rate will be elevated by atrial pacing to a base rate to 100 bpm or maximally tolerable rate (less than 10% drop in  $dP/dt_{max}$  from baseline no pace), to ensure a constant heart rate. The RV-LV (= VV-timing) intervals will be zero. Optimal AV-delay will be calculated using formulas ( $PAV_{ECG} = \min \{Ap-Pend + 30 \text{ ms}, Ap-RVs - 50 \text{ ms}\}$ ) derived

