## 8 Statistical Method and Data Analysis

### 8.1 Sample Size Justification

This study is powered for non-inferiority for the primary end point of difference in percentage change dP/dt max from baseline between Biventricular (BiV) pacing and Quadri-ventricular (Multispot) pacing. This is calculated as [percentage change in dP/dt max during Multispot] - [percentage change in dP/dt max during BiV]. Non-inferiority will be declared if the lower limit of a 1-sided 97.5% confidence interval of difference does not fall below -4%. Assuming the expected difference in percentage change dP/dt max between BiV pacing and multispot pacing is 0% and a standard deviation in differences of 8%, 34 patients would have 80% power to demonstrate non-inferiority for dP/dt max. The total sample size is increased to 40 patients to accommodate for non-compliance with protocol. Superiority testing will be performed if non-inferiority is met.

$$\begin{aligned}H_0: \Delta_{\text{multispace}} - \Delta_{\text{BiV}} &\leq -4\% \\H_1: \Delta_{\text{multispace}} - \Delta_{\text{BiV}} &> -4\%\end{aligned}$$

Previous literature suggests the average mean difference in percentage change between BiV and no pacing is 18%, in this study we consider Multispace non-inferior to BiV if the difference in their means is less than a quarter of the difference between BiV and no pacing [34]. No literature is available on the standard deviation of differences, which is the variability of the difference between pacing configurations within each subject. However we estimate that it would be less than half the variability seen when comparing differences across different patients.

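### Multispot is always paced after its proximal BiV comparator, so the primary contrast is exposed to drift unless each run is referred to its adjacent AAI run, which 8.2 and 8.3 do not specify

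*Combined protocol and SAP*

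**What the plan says.** Section 2 names RV plus the proximal lateral electrode as the reference (standard CRT) and the three-electrode lateral setting as the main assessment. In Figure 4, Protocol (First part), the reference is step "C) Pacing @ proximal electrode. Make sure capture is obtained. If yes, run pacing protocol". It is followed directly by "D) Simultaneous pace @ all three electrodes". The figure legend says this part is alike for all patients and that only the second part depends on anatomy. No section randomizes, counterbalances or records the order.

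Within each setting the optimal AV delay comes first, and then: "Program other AV delays (+/- 20 ms & +/- 40 ms) and repeat pacing protocol". Each paced run of 10–15 s alternates with 10–15 s of AAI pacing, four times per AV delay.

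Section 6.4 says that "study measurements have been designed to minimize the impact of within-subject temporal variation". Section 8.1 powers the trial on the difference in percentage change from baseline, with the rule: "Non-inferiority will be declared if the lower limit of a 1-sided 97.5% confidence interval of difference does not fall below -4" percent. Section 8.2 defines the primary endpoint as the dP/dt max value during the two kinds of pacing. Section 8.3 models the mean dP/dt max difference with terms for center, configuration, AV delay and, if possible, heartbeat.

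**The concern.** In a within-patient comparison, order is the main route by which time can bias the contrast. Here the test setting follows its comparator in every patient. A drift with a non-zero mean across patients therefore shifts the estimate by a fixed amount, which a larger sample does not remove. A period term added afterwards would not help, because step and configuration coincide. The one safeguard in the design is the alternating AAI run, and it works only if it enters the analysis. Sections 8.2 and 8.3 do not say that it does. Section 8.1 does not say which baseline is the denominator: 7.4.2 uses the word both for the interleaved AAI runs and for the unpaced state, and 8.1 justifies the margin against no pacing.

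At stake are the non-inferiority claim and the superiority test that 8.1 adds if non-inferiority is met.

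**Working it through.** **Inputs from 8.1.** Margin 4 points, one-sided alpha 0.025, "a standard deviation in differences of 8" percent, true difference 0 ("the expected difference in percentage change dP/dt max between BiV pacing and multispot pacing is 0" percent). Stated result: "34 patients would have 80% power to demonstrate non-inferiority for dP/dt max".

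**The plan's own figure.** For a paired t-test, power = P(T > t(0.975, n−1)), where T is noncentral t with n−1 df and noncentrality d/(8/√n). At n = 34 the standard error is 8/√34 = 1.372. With d = 4 the noncentrality is 4/1.372 = 2.92 and power is 0.808. At n = 33 power is 0.795, so 34 is reproduced. At n = 40 power is 0.869.

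**Time between comparator and Multispot.** One on/off cycle lasts 20–30 s.
- Five AV delays × 4 cycles × 20–30 s = 400–600 s, or 6.7–10 min. This is the gap between matched proximal and Multispot runs, before any reprogramming time.
- It is near the upper end, since 7.4.2 allows up to five AV delays and about four repetitions. With one AV delay the gap would be 4 × 20–30 s = 1.3–2 min.

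**What a drift does to the contrast.** The documents give no drift size. I assume a 1% or 2% change between the two settings, an AAI baseline of 1000 units, the 18% BiV effect quoted in 8.1, and no true difference between configurations.

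| Drift between settings | Raw value or single initial baseline | Adjacent AAI run |
|---|---|---|
| Proportional, +1% | 1180 × 0.01 / 1000 = 1.2 points | 0 |
| Proportional, +2% | 1180 × 0.02 / 1000 = 2.4 points | 0 |
| Additive, +10 units | 10/1000 = 1.0 point | 1190/1010 − 1.18 = −0.18 points |
| Additive, +20 units | 20/1000 = 2.0 points | 1200/1020 − 1.18 = −0.35 points |

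Raw differences are expressed as points of the initial baseline. With adjacent baselines the sign reverses: an upward additive drift works slightly against Multispot.

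**What a bias b does to the test (n = 34, SD 8).** If b favours Multispot and the true difference is −4, the false non-inferiority rate is the power formula with d = b. If b runs against Multispot and the true difference is 0, power is the formula with d = 4 − b.

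| b (points, assumed) | b/1.372 | False non-inferiority rate | Power if b is against Multispot |
|---|---|---|---|
| 0 | 0 | 0.025 | 0.808 |
| 0.5 | 0.36 | 0.054 | 0.697 |
| 1 | 0.73 | 0.105 | 0.565 |
| 2 | 1.46 | 0.293 | 0.293 |

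The false superiority rate in Multispot's favour at a true difference of 0 takes the same values as the third column. For comparison, downward additive drift of 10 or 20 units with adjacent baselines leaves +0.18 or +0.37 points, and the false non-inferiority rate is then about 3.3% or 4.5%.

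**Effect of the fix on size.** I treat the contrast as a balanced two-order comparison with a period term (n−2 df), a simplification of the full model. The requirement stays at 34 (power 0.807), and power at 40 is 0.869. If order is randomized but period is left out, the SD becomes √(64 + b²). The requirement is then 34, 36, 38 or 42 for b = 1, 2, 3 or 4, so the planned 40 suffice up to b = 3.

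**The case against.** The strongest reply is that the design already deals with drift. Paced and AAI runs alternate every 10–15 s at a constant atrial-paced rate, and 8.1 states the hypotheses and margin as percentage change from baseline. On that reading proportional drift cancels and additive drift of 1–2% leaves 0.2–0.4 points. This stands, and it makes the 10–29% range conditional. It does not close the point, because 8.2 and 8.3 describe raw dP/dt max and no section ties baseline to the adjacent AAI run.

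Several stronger readings are tempting and not supported:
- A reader might infer that any drift is credited to Multispot in every patient. The order fixes when Multispot is tested, not which way a patient drifts. Drift of mixed sign adds variance, which more patients do reduce.
- A reader might infer that pacing the optimal AV delay first confounds the primary contrast. It comes first in both configurations, so it can bias the AV-delay comparison but not Multispot minus BiV at matched AV delay. The order of the other four delays is not stated.
- A reader might infer that the whole session has one fixed order that a switch could randomize. Only the four lateral steps are common to all patients. The second part depends on anatomy and needs a lead moved or added, and AV delay is set on the master pacer (4.1), not on the connection box.
- A reader might infer that the statement in 6.4 is false. It claims to minimize temporal variation, and the alternation does reduce it.

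**Conclusion.** The point holds in a conditional form. As listed, Multispot follows its comparator by about 7–10 min in every patient, and neither design nor model accounts for order. If raw values or a single initial baseline are used, an assumed systematic bias of 1–2 points, 25–50% of the 4-point margin, raises the false non-inferiority rate from 2.5% to 10–29% or lowers power from 81% to 56–29%. These figures rest on n = 34, SD 8 and an assumed bias that the documents neither give nor rule out. With percentage change from the adjacent AAI run, slow drift is largely removed. Carryover, time-varying response to pacing and catheter movement are then left, of unknown size, and only a varied order guards against attributing their average effect to Multispot. The change is worth making because it is cheap and because step order cannot be separated from configuration once the data are collected.

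**What to change.** 1. In 7.4.2 and Figure 4, confirm capture at all lateral electrodes first. Then run steps A–D in a randomized or counterbalanced order per patient, for example from a 4×4 Williams square on a pre-printed list. The four steps use electrodes in one vein, and 4.3 describes connection-box channels that switch individually, so no lead has to move for this. The parts that need a lead repositioned or added keep their practical order.
2. Record the order actually used and add a period term to the 8.3 model.
3. State in 8.1 to 8.3 that the primary variable is percentage change from the adjacent AAI run, and align the 8.2 endpoint and 8.3 model with the 8.1 hypotheses. This step removes most slow drift. Randomizing the order does not replace it.
4. Optionally, vary the order of the AV delays within a setting. This protects the AV-delay comparison only.

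Cost: protocol wording, a printed list and slightly more operator attention. No additional paced runs, equipment or patients are needed. Where an electrode does not capture, the sequence will be incomplete, and the plan should say how such patients enter the model.

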**PROTOCOL (Second part)**

RePlace "Multi-electrode lead" in anterior vein position  
Add a second lead in the posterior vein

Start RA-pacing (100 bpm or otherwise highest tolerable rate)

(A) Pacing @ distal electrode. Make sure capture is obtained. If yes, run pacing protocol

(B) Pacing @ mid electrode. Make sure capture is obtained. If yes, run pacing protocol

(C) Pacing @ proximal electrode. Make sure capture is obtained. If yes, run pacing protocol

(D) Simultaneous pace @ all three electrodes  
Run pacing protocol

D

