## 2 Study Summary

This clinical trial is an exploratory, prospective, interventional, non-randomized multi-center research study assessing augmentation of contractility using

positive left ventricular (LV) dP/dt max across LV pacing site(s) in patients indicated for cardiac resynchronization therapy (CRT).

During a research study, an electrophysiological (EP)-exploratory procedure or prior to CRT-implant, a venogram will be obtained to identify the target vessels for LV stimulation. Leads will be placed (temporarily) in three coronary veins; in the anterior, posterior and lateral branches. No more than two left ventricular leads will be placed at the same time.

Three LV pacing configurations will be evaluated:

- Biventricular pacing (BiV: 1 RV lead and 1 LV lead),
  - Tri-ventricular pacing (Multivein: 1 RV lead and 2 LV leads) or
  - Quadri-ventricular pacing ( MultiSpot: 1 RV lead 1 LV catheter with LV pacing spots)
- and the corresponding positive LV dP/dt max will be measured.

BiV pacing will be performed at each of the three coronary veins. The total number of BiV settings is 5 being:

- **RV – LV Lateral – Proximal (Reference: Standard CRT)**
- RV – LV Lateral – Mid
- RV – LV Lateral – Distal
- RV – LV Posterior
- RV – LV Anterior

Multivein-pacing will be performed in the posterior and anterior target vessels (in each vein one spot). There is only one multivein-setting, being:

- RV – LV Anterior – LV Posterior

Multispot-pacing will be performed using an EP catheter at the “normal” LV lead implant site (i.e., (postero)-lateral target vessel). There is only one Multispot-setting tested, being:

- RV – LV Lateral Proximal – LV Lateral Mid – LV Lateral Distal  
(Main Assessment)

Within this study the total number of settings is 7, using three lead configurations (see also Figure 1).

[figure not shown]

**Figure 1: Figure depicting the different ventricular lead positions.** Only two coronary sinus leads will be placed simultaneously. The EP-catheter used for the (postero)lateral coronary vein may be repositioned in the posterior coronary vein or vice versa. Pacing protocol includes synchronized pacing from the RV and LV electrode(s). Up to three “spots” in the LV lateral vein will be paced simultaneously.

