**PROTOCOL ( Alternative Second part)**

Leave "Multi-electrode lead" (postero)lateral vein position  
Add a second lead in the posterior or anterior vein

Start RA-pacing (100 bpm or otherwise highest tolerable rate)

(A) Pacing @ distal electrode. Make sure capture is obtained. If yes, run pacing protocol

(B) Pacing @ mid electrode. Make sure capture is obtained. If yes, run pacing protocol

(C) Pacing @ proximal electrode. Make sure capture is obtained. If yes, run pacing protocol

(D) Simultaneous pace @ all three electrodes  
Run pacing protocol

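### As extracted, the Figure 4 second-part step lists repeat the lateral-vein steps and contradict the posterior BiV and Multivein settings that the protocol defines elsewhere

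*Combined protocol and SAP*

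**What the plan says.** Section 2 fixes what is to be measured: "Within this study the total number of settings is 7, using three lead configurations". Three of these settings use the anterior or posterior vein: BiV from the anterior vein, BiV from the posterior vein, and the only Multivein setting, "RV – LV Anterior – LV Posterior". Section 2 adds: "Multivein-pacing will be performed in the posterior and anterior target vessels (in each vein one spot". The body of Section 7.4.2 agrees: "The leads placed in the alternative veins I and II will be stimulated separately or simultaneously (multi-vein; uni-spot". The Figure 1 legend in Appendix A lists the same settings. The Figure 4 caption describes one of the two parts as BiV or Multivein pacing from one or both of two opposing veins.

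The step boxes of Figure 4 read differently. The second part moves the multi-electrode lead to the anterior vein and instructs: "Add a second lead in the posterior vein". The first step is then "A) Pacing @ distal electrode. Make sure capture is obtained. If yes, run pacing protocol". The same instruction follows for the mid and proximal electrodes, and the last step is "D) Simultaneous pace @ all three electrodes". The alternative second part leaves the multi-electrode lead in the lateral vein, instructs "Add a second lead in the posterior or anterior vein", and lists the same four steps. All of these steps match those of the first part, where they correctly give the three lateral BiV settings and Multispot.

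**The concern.** The second-part box adds a posterior lead and never tells the operator to pace it. A site that took the box literally would run three anterior BiV spots and an anterior three-electrode setting. It would record neither posterior BiV nor Multivein.

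The first two secondary objectives compare Multivein with standard BiV and with Multispot. The correlation and best-configuration objectives draw on all three configurations. A missed run could not easily be recovered: the measurement is made in one invasive session, subjects exit before hospital discharge with no further follow-up (Section 7.5), and no imputation is planned (Section 8.3). The loss would not show in the size of the Analysis Population either, because a patient with only BiV and Multispot meets its rule of two configurations out of three (Section 8.4).

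**Working it through.** **1. The plan's own figure.** Section 8.1 gives a margin of 4%, an expected difference of 0%, an SD of differences of 8%, one-sided alpha 0.025 and 80% power.
- Normal approximation for paired data: n = ((1.96 + 0.84) × 8/4)² = 31.4, so 32.
- Noncentral t: power is 79.5% at n = 33 and 80.8% at n = 34, so 34. This reproduces the plan. At n = 40 the power is 86.9%.
- The figure concerns Multispot against BiV. Both come from the first part, so it does not depend on the second-part boxes.

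**2. Required settings against the boxes, read literally.**

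| Setting in Section 2 | First + second part | First + alternative |
|---|---|---|
| Lateral proximal BiV (reference) | yes | yes |
| Lateral mid BiV | yes | yes |
| Lateral distal BiV | yes | yes |
| Lateral Multispot | yes | yes |
| Anterior BiV | yes (three spots, not one) | no |
| Posterior BiV | no | no |
| Multivein | no | no |
| **Covered** | **5 of 7** | **4 of 7** |

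Each route has 4 + 4 = 8 paced steps. In the first route, 8 − 5 = 3 runs fall outside the seven settings: two extra anterior spots and one anterior three-electrode run. In the alternative route, the second four steps repeat lateral settings already recorded.

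**3. Can the last step be read as Multivein?** There are two charitable readings.
- The three electrodes could be RV, anterior and posterior. But the preceding steps of the same box name distal, mid and proximal electrodes, and the identical words in the first part mean three spots in one vein. Posterior BiV would still be missing.
- The step could mean the three anterior electrodes plus the posterior lead. That makes 3 + 1 = 4 LV spots, and Section 4.1 describes a system that paces up to three.

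**4. Can the alternative layout give Multivein?** It places leads in the lateral vein and in one of the other two. The defined setting needs anterior and posterior together, so the layout cannot give it, whatever steps are listed.

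**5. Time.** One run is 5 AV delays × 4 repetitions × 20–30 s (10–15 s on plus 10–15 s off) = 400–600 s, or 6.7–10 min. Seven runs take 46.7–70 min and eight take 53.3–80 min. The net addition is 8 − 7 = 1 run, about 7–10 min, against a stated procedure time of 60–120 min. Section 7.4.2 allows up to five AV delays, so these are upper figures.

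**The case against.** The strongest reply is that the protocol plainly does plan Multivein. Section 2, the body of Section 7.4.2, Appendix A and the caption of Figure 4 itself all call for it, and the second-part box puts the leads in the right veins. Nothing gives the boxes precedence over the text. In Section 7.4.2 the pointer to Figure 4 is attached to the Multispot sentence, not to the multi-vein one. Section 6.4 requires training and adherence to the whole plan, and Section 7.4.2 allows sponsor staff to support procedures. All of this stands, and it makes the loss conditional on a site working from the boxes alone.

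The boxes were also read by a program from a figure that is only partly shown. The placement lines differ sensibly between boxes while the steps are identical, which suggests copied text, but the extraction cannot settle the matter. The original figure has to be checked first.

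A reader might infer more than the documents support:
- That the trial will have no Multivein data, or that data will be missing by site. Which source sites would follow is not stated.
- That second-part recordings will be mislabelled as Multivein. No labelling scheme is given.
- That three runs outside the seven cost 20–30 min. That is a gross figure; two required runs are omitted, so the net is one run.
- That the primary analysis is weakened. Its data come from the first part.

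**Conclusion.** There is a contradiction within the protocol. As extracted, the step lists for the second part and its alternative do not contain two settings that Section 2, Section 7.4.2 and Appendix A require: posterior BiV and Multivein. The alternative list omits anterior BiV as well, and its layout cannot produce the defined Multivein setting. Taken literally, the boxes supply no Multivein dP/dt max for two secondary comparisons and leave the correlation and best-configuration analyses without their third configuration.

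This rests on two assumptions: that the extracted boxes match the original figure, and, for any actual loss of data, that a site follows the boxes rather than the text. The primary comparison, the 34 patients behind it and the total of 40 are unaffected. Severity is should-fix: it is an operational step list that conflicts with the plan, its reach is limited to secondary objectives of an exploratory study, and it is cheap to correct before measurements are made.

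**What to change.** Check the original Figure 4. If its boxes read as extracted, reconcile the second-part and alternative step lists with Section 2, Section 7.4.2, the figure's own caption and the Figure 1 legend in Appendix A, so that the lists contain the settings the protocol already defines. No new setting is needed.

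State in Section 8.3 whether recordings from the alternative layout count as Multivein in the analysis or are reported separately. Section 2 defines only the anterior-plus-posterior pair as Multivein.

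The cost is a correction to one figure, a sentence in the analysis section, and making sure that site training reflects the change. A step list matching the seven settings would have one run fewer than the eight now listed.
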